### **Height Outcome Measures**

Efficacy will be assessed as the change in annualized growth velocity from the baseline period (screening to Visit Day 1) to the intervention period (Visit Day 1 to 12 Month Visit). Efficacy will also be assessed as the change in height SDS from Visit Day 1 to 12 Month Visit. Height SDS will be calculated using the CDC growth curves and growth velocity SDS will be based on the Bone Mineral Density in Childhood Study. In subjects with hypochondroplasia or *ACAN* mutations, an adequate response to therapy will be considered an increase in annualized growth velocity of  $\geq 1.6$  cm/year based on the adjusted mean response to vosoritide in the Phase III trial in patients with achondroplasia which is clinically significant. In subjects with a Rasopathy, *SHOX* mutation, *NPR2* mutation or *CNP* deficiency, an adequate response to therapy will be considered an increase in annualized growth velocity of  $\geq 3$  cm/year (see details in inclusion criteria). Growth velocity and change in height SDS will be calculated on an annual basis during the extension phase of the study.

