#### **Endpoints:**

The primary study endpoints include:

- Incidence of adverse events per subject with particular attention to Grade 3 and 4 adverse events as well as to rates of hypotension
- Change from baseline in age-sex standardized annualized growth velocity after 12 months of treatment
- Change from baseline in age-sex standardized height SDS after 12 months of treatment

The secondary study endpoints include:

- Change from baseline in seated height ratio after 12 months of treatment
- Change from baseline in arm span minus standing height after 12 months of treatment
- Change from baseline in bone age/chronological age after 12 months of treatment

During the extension study, all of the endpoints will remain the same, but the timeframe will be extended from 12 months until growth cessation or subject withdrawal from the study.

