| 
The primary objectives of the study are as follows:
 
 
To evaluate the safety and tolerability of daily subcutaneous (SC) injections of vosoritide administered for 12 months in patients with selected genetic causes of short stature
 
To evaluate the change from baseline in age-sex standardized annualized growth velocity after 12 months of daily SC injections of vosoritide in patients with selected genetic causes of short stature
 
To evaluate the change from baseline in age-sex standardized height standard deviation score (SDS) after 12 months of daily SC injections of vosoritide in patients with selected genetic causes of short stature
 
 | 
The primary study endpoints include:
 
 
Incidence of adverse events per subject with particular attention to Grade 3 and 4 adverse events as well as to rates of hypotension
 
Change from baseline in age-sex standardized annualized growth velocity after 12 months of treatment
 
Change from baseline in age-sex standardized height SDS after 12 months of treatment
 
 | 
The rates of adverse events will describe the safety profile of vosoritide in this study population.
 
Change in annualized growth velocity and height SDS are standard measures of efficacy of growth promoting agents. They are highly correlated but as height velocity differs by age and gender, the height SDS takes these factors into account.
 |

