### 5 STUDY POPULATION

#### 5.1 INCLUSION CRITERIA

Inclusion and exclusion criteria will be pre-screened based on information provided by the referring clinician. All inclusion and exclusion criteria will then be verified at the screening visit and official screening laboratory studies will be performed as part of that visit. There will be no birth weight or length inclusion or exclusion criteria.

In order to be eligible to participate in this study, an individual must meet all of the following criteria:

1. Parent(s) or guardian(s) are willing and able to provide written, signed informed consent after the nature of the study has been explained and prior to performance of any research-related procedure. Also, subjects under the age of 18 are willing and able to provide assent (if required) after the nature of the study has been explained and prior to performance of any research-related procedure.
2. Stated willingness to comply with all study procedures and availability for the duration of the study
3. Age  $\geq 3$  years 0 days AND  $\leq 10$  years 364 days for males,  $\leq 9$  years 364 days for females
4. Pre-pubertal defined as Tanner Stage 1 breasts in females and testicular volumes  $\leq 3$  cc in males. This must be confirmed at the Day 1 visit prior to initiation of vosoritide.
5. Patient height  $\leq -2.25$  SDS. All height SDS values are calculated using the CDC growth charts/data tables.

6. Patients with pathogenic or likely pathogenic variants in genes known to cause the specific genetic subgroups of short stature listed below are eligible for inclusion in the study. Pathogenicity of variants will be classified as per the American College of Medical Genetics criteria with the exception of *ACAN* mutations as detailed below. Documentation of the presence of the variant must be obtained using a lab results report from a CLIA certified laboratory. Classification of the variant's pathogenicity status will be performed by the Children's National study team.
- A. CNP deficiency due to mutations in *NPPC* – Subjects with heterozygous or homozygous defects in *NPPC* are eligible.
  - B. Hypochondroplasia – Subjects with heterozygous variants in *FGFR3* gene associated with hypochondroplasia are eligible. Subjects with variants in *FGFR3* known to cause achondroplasia or thanatophoric dysplasia or SADDAN syndrome will be excluded.

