### 9.1 STATISTICAL HYPOTHESES

- Primary Safety Endpoint(s): We will rule out safety concerns. That is, we will rule out the null hypothesis that risk of adverse events post-drug administration will be more than twice the risk during the baseline period (i.e, RR or OR > 2).
- Primary Efficacy Endpoint(s): The null hypothesis is that there is no change from baseline in annualized growth velocity or height SDS over the 12 months of intervention when compared to the 6 month baseline observation period. The alternate hypothesis is that there is a change from baseline in these values.
- Secondary Efficacy Endpoint(s): The null hypothesis is that there is no change from baseline in seated height ratio, arm span minus standing height, or bone age divided by chronological age over the 12 months of intervention when compared to the 6 month baseline observation period. The alternate hypothesis is that there is a change from baseline in these values.

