#### 9.4.2 ANALYSIS OF THE PRIMARY EFFICACY ENDPOINT(S)

Growth velocity, based on anthropometric measures, at each scheduled time point will be summarized using descriptive statistics (mean, SD, median, interquartile range, minimum, and maximum). The test of hypothesis of no change from the baseline in growth velocity and height SDS will be conducted via paired t-test. The measurement of height will be converted to age-and sex-appropriate standard score (SDS) by comparison with the CDC reference standards. The Z-score will be summarized similarly to growth velocity. Additional details of the analysis including management of missing data, and approach to handling outliers, non-adherent and lost to follow up subject data will all be included in a separate statistical analysis plan.

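### The primary growth-velocity endpoint is named as age-sex standardised, but the sections that define and test it describe velocity without standardisation

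*Protocol*

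**What the plan says.** The endpoint list in the Synopsis (Section 1.1) gives the primary velocity endpoint as "Change from baseline in age-sex standardized annualized growth velocity after 12 months of treatment". The objectives in the Synopsis and the table in Section 3 use the same standardised form.

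The sections that put the endpoint to work drop the standardisation:

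- Section 8.1, Height Outcome Measures: "Efficacy will be assessed as the change in annualized growth velocity from the baseline period (screening to Visit Day 1"), compared with Day 1 to the 12 Month Visit.
- Section 9.1: "The null hypothesis is that there is no change from baseline in annualized growth velocity or height SDS over the 12 months of intervention". Here SDS is attached to height only.
- Section 9.4.2: "The test of hypothesis of no change from the baseline in growth velocity and height SDS will be conducted via paired t-test". The only conversion to a score described there is for height, and the section adds "The Z-score will be summarized similarly to growth velocity".

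Section 8.1 also states that "growth velocity SDS will be based on the Bone Mineral Density in Childhood Study". Section 3 justifies the two efficacy endpoints by noting that "height velocity differs by age and gender, the height SDS takes these factors into account".

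On puberty, inclusion criterion 4 in Section 5.1 requires pre-pubertal status and adds "This must be confirmed at the Day 1 visit prior to initiation of vosoritide". The Schedule of Activities records Tanner stage at Day 1, Month 6 and Month 12.

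**The concern.** A primary endpoint should have one definition. Here the same endpoint carries two, and they are different variables that can give different results from the same heights. The trial is open-label with a single arm, so choosing the scale after the data are seen would be hard to defend.

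The choice also has substance. Each child serves as his or her own control, and the child is older in the treatment window than in the baseline window. Raw velocity makes no allowance for that, whereas velocity SDS does, as far as the reference describes these children. Section 3 itself recognises that velocity depends on age and sex.

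**Working it through.** **The wording, side by side.** Two places (Synopsis, Section 3) call the velocity endpoint standardised. Three places (8.1, 9.1, 9.4.2) give it without standardisation. In 9.4.2 the Z-score is spoken of as something apart from growth velocity, which fits only if velocity there is not a Z-score. The justification in Section 3 credits height SDS, and not velocity, with taking age and sex into account. The one counter-statement is the velocity-SDS reference in 8.1, which no hypothesis, test or summary uses.

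The protocol states no sample size calculation, alpha or SD for this endpoint, so there is no planned figure to reproduce.

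**The age gap between the windows** (visit windows of two weeks ignored).

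- Baseline runs from -6 months to Day 1, with midpoint -3 months.
- Treatment runs from Day 1 to +12 months, with midpoint +6 months.
- Gap = 6 - (-3) = 9 months = 0.75 year.

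**Shift in raw velocity from ageing alone.** Shift = gap × change in velocity per year of age. The protocol gives no slope. I assume a pre-pubertal fall of 0.2 to 0.6 cm/year per year of age:

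- 0.75 × (-0.2) = -0.15 cm/year
- 0.75 × (-0.6) = -0.45 cm/year

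For scale only, against the individual response criteria in Sections 5.1 and 8.1:

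- 1.6 cm/year (hypochondroplasia, *ACAN*): 0.15/1.6 = 9% and 0.45/1.6 = 28%
- 3 cm/year (the other four groups): 0.15/3 = 5% and 0.45/3 = 15%

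**What such a shift does to the paired test.** Assume no drug effect, N = 75, two-sided alpha 0.05, and an SD of the paired change of 1.5 to 2.5 cm/year; alpha and SD are assumptions. With SE = SD/√75 and z = |shift|/SE, the rejection rate is Φ(z - 1.96) + Φ(-z - 1.96).

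| Shift (cm/year) | SD | SE | z | Rejection rate |
|---|---|---|---|---|
| -0.15 | 2.5 | 0.289 | 0.52 | 8% |
| -0.15 | 1.5 | 0.173 | 0.87 | 14% |
| -0.45 | 2.5 | 0.289 | 1.56 | 34% |
| -0.45 | 1.5 | 0.173 | 2.60 | 74% |

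These rejections lie mainly in the direction of a decrease. In the presence of a true benefit, the same shift would reduce the estimate.

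**Puberty.** Baseline is pre-pubertal by rule and the treatment year is not. The age limit applies at screening, 18 months before Month 12, so boys can be almost 11 + 1.5 = 12.5 years and girls almost 10 + 1.5 = 11.5 years at that visit. If 10% to 20% of children entered puberty and gained 1 cm/year averaged over the year (both assumed), the pooled mean would move by +0.1 to +0.2 cm/year. Taken with the ageing range, the net runs from -0.45 + 0.10 = -0.35 to -0.15 + 0.20 = +0.05 cm/year.

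**The case against.** The strongest reply is that the short form is shorthand. No section calls the tested variable raw or gives the primary test in cm/year. Within one row of the Section 3 table the endpoint is named as standardised and its justification uses the short form, so 8.1, 9.1 and 9.4.2 may do the same. The velocity-SDS reference in 8.1 has an obvious use in the primary endpoint. This stands to a degree: a reader might infer that the protocol plainly tests raw velocity, and it does not say so. Raw velocity is the more natural reading of 9.4.2, but standardisation is not absent from the plan.

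A second reply is that analysis detail is left to the SAP. Section 9.4.2 defers missing data, outliers, non-adherence and loss to follow-up. The scale of the primary endpoint is different, because the protocol already states it in conflicting ways and any SAP would have to depart from one set of sections. For a puberty analysis the reply does stand. A Tanner-based sensitivity analysis is ordinary SAP content, and its absence here is no error.

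A third reply is that height SDS, the other primary efficacy endpoint, is already standardised, and that the trial is exploratory and looks to a later randomised study to prove efficacy. This limits the consequence but does not settle which velocity result is primary.

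**Conclusion.** The inconsistency is real and should be corrected. The protocol does not fix whether the primary velocity variable is an SDS or cm/year, and taken literally 9.4.2 tests the raw variable. The gap of 0.75 year between window midpoints follows from the design. The shift of -0.15 to -0.45 cm/year and the rejection rates rest wholly on assumed slopes, SDs and alpha.

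Three stronger readings are not supported. First, a reader might infer that the wording favours the drug. On the assumptions above the net is -0.35 to +0.05 cm/year, mostly against it; other assumptions could change the sign, and the documents supply none. Second, a reader might infer that velocity SDS would also deal with puberty. The cited reference is age-based by its title, so it does not follow each child's pubertal timing, and height SDS has the same limit. Third, a reader might infer that children who enter puberty should be removed from the primary analysis. That would select on a post-baseline variable and depart from the all-dosed population of Section 9.3. Nor would velocity up to the last Tanner 1 visit serve, since a child at Tanner 2 by Month 6 would have no on-treatment velocity left.

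**What to change.** In Sections 8.1, 9.1 and 9.4.2, state that the tested primary variable is the change in growth-velocity SDS, using the reference already named in 8.1, and that the change in cm/year is reported as supportive. In 9.4.2, describe the conversion of velocity to a score as is done for height. This is a change of wording and needs no new data. The reference is for annual velocity while the baseline spans six months, so the SAP should say how that interval is scored.

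Optionally, add one supportive sensitivity analysis restricted to children still at Tanner stage 1 at Month 12, using the staging already scheduled. It would have fewer subjects and would select on a post-baseline variable, so the all-dosed analysis stays primary.

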### **Pharmacokinetic Variables**

During the Day 1 and 6 and 12 month visits, PK plasma samples are collected pre-dose and at 5 ( $\pm 2$  min), 15 ( $\pm 2$  min), 30 ( $\pm 5$  min), 60 ( $\pm 5$  min), 90 ( $\pm 5$  min), 120 ( $\pm 5$  min) min, and 180 ( $\pm 5$  min) min post-dose.

The following PK parameters will be estimated by non-compartmental analysis for Day 1 and 6 and 12 Months:

- Area under the plasma concentration-time curve from time 0 to infinity ( $AUC_{0-\infty}$ )
- Area under the plasma concentration-time curve from 0 to the time of last measurable concentration ( $AUC_{0-t}$ )
- $C_{max}$
- $T_{max}$
- Elimination half-life ( $t_{1/2}$ )
- Apparent clearance of drug ( $CL/F$ )
- Apparent volume of distribution based upon the terminal phase ( $V_z/F$ )

Samples for PK markers will be sent to BioMarin or their designated contracted laboratory for analysis. Details of processing and shipping will be in the Laboratory Manual. In brief, the samples will be labeled with a coded ID number as well as with the date and time of collection. The will be placed on ice and serum will be separated. A protease inhibitor will be added to prevent degradation of vosoritide.

Samples will then be stored in [name] research laboratory until shipment. BioMarin or the designated laboratory will return all unused samples to Children's National after completion of PK analyses.

### **Pharmacodynamic Markers**

Samples will be obtained for urinary cGMP, if available, at baseline at the Screening Visit and at baseline and 1 hour, 2 hours and 4 hours post vosoritide injection at the Day 1 Visit, 6 Month Visit and 12 Month Visit. Each time point will have a +/- 15 minute window. Children will not be catheterized. If they are unable to void at the specified time, that sample will be skipped. Urine creatinine samples will be obtained at all of the same time points. Serum collagen X marker measurement will be obtained at baseline at the Screening Visit, Day 1 Visit, 6 Month Visit and 12 Month Visit and all in-person extension phase visits. Assays for PD markers will be done at outside research laboratories. Details of the specific laboratories, processing needs, and shipping instructions will be in the Laboratory Manual. Coded samples will be provided with the date and time of collection. Remaining samples will be destroyed after assay completion.

### **DXA scan**

DXA scans will be performed as per routine clinical protocols at Children's National Hospital and will include whole body less head as well as a lumbar spine DXA. The amount of radiation from a standard DXA is 0.013 mSv. DXA scans will be done every 24 months during the extension phase of the trial.

### **QoLISSY Scale Measurements**

QoLISSY, the Quality of Life in Short Stature Youth, is a validated questionnaire that includes modules for both parents and children. We will administer both modules (as age appropriate) at the Screening Visit, Day 1 Visit, 6 Month Visit and 12 Month Visit and all in-person extension phase visits. The instrument will be scored as per the user manual's instructions.

## **8.2 SAFETY AND OTHER ASSESSMENTS**

### **Health events**

Health events (medical issues that result in a hospital admission or trip to the emergency department, other significant medical issues, and changes in the participant's health status including changes to prescription medications) will be reviewed at the time points indicated in the Schedule of Activities (**Section 1.3**) and recorded on a case report form (CRF). To assist participants' parents in recalling health events, they will be provided with a Health Events Diary on which they can record health events experienced by their child. Updates to concomitant medications will be captured on the appropriate CRF. Should the occurrence of an adverse event (AE) or serious adverse event (SAE) come to the attention of study personnel during review of health events, it will be captured on the appropriate CRF.

### **Physical Examination and Tanner Staging**

Physical examination will include assessment of general appearance; cardiovascular; dermatologic; head, eyes, ears, nose, and throat; lymphatic; respiratory; GI; musculoskeletal; and neurological/psychological and genitourinary. Tanner stage will also be assessed. All physical examinations will include a detailed musculoskeletal examination that will include palpation of bone structures and joints for tenderness and assessment of mobility and gait to monitor risk of bone overgrowth. If concerns of bone overgrowth arise, referral will be made to an orthopedist for further clinical evaluation including radiographic evaluation. The Screening Visit results will be the baseline

values and clinically significant changes from baseline will be recorded as an AE or SAE as appropriate. A qualified medical provider (either physician or NP) will perform the physical examination.

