### 1.3 SCHEDULE OF ACTIVITIES (SOA)

| Procedure                                                      | Screening and Initiation of Observation (-6 months) | Monthly Phone calls +/- 4 days (Months -5 through -1) | Day 1 visit (6 months +/- 2 weeks after screening) | Day 2 Visit | Days 3 through 5 Followed by Bi-weekly Phone calls +/- 4 days (Months 1 through 5) | 6 month visit (+/- 2 weeks) | Monthly Phone calls +/- 4 days (Months 7 through 11) | 12 month visit (+/- 2 weeks) | Early termination |
|----------------------------------------------------------------|-----------------------------------------------------|-------------------------------------------------------|----------------------------------------------------|-------------|------------------------------------------------------------------------------------|-----------------------------|------------------------------------------------------|------------------------------|-------------------|
| Informed consent                                               | X                                                   |                                                       |                                                    |             |                                                                                    |                             |                                                      |                              |                   |
| Medical History                                                | X                                                   |                                                       | X                                                  |             |                                                                                    |                             |                                                      |                              |                   |
| Parental anthropometrics a                          | X                                                   |                                                       |                                                    |             |                                                                                    |                             |                                                      |                              |                   |

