| Physical examination including a complete musculoskeletal exam | X                                                   |                                                       | X                                                  |             |                                                                                    | X                           |                                                      | X                            | X                 |
| Tanner stage                                                   | X                                                   |                                                       | X                                                  |             |                                                                                    | X                           |                                                      | X                            | X                 |
| Vital signs b                                       | X                                                   |                                                       | X                                                  | X           |                                                                                    | X                           |                                                      | X                            | X                 |
| Anthropometric measurements c                       | X                                                   |                                                       | X                                                  |             |                                                                                    | X                           |                                                      | X                            | X                 |
| ECG                                                            | X                                                   |                                                       | X                                                  |             |                                                                                    | X                           |                                                      | X                            | X                 |

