#### Individual Subject Stopping Criteria

Dosing for the subject will be temporarily discontinued and DSMB will be informed (at a minimum) if any of the following occur:

- Any treatment emergent adverse event (TEAE) at least Grade 3 (according to the most current version of the CTCAE) assessed by the PI determined to be related to the study drug
- Any two TEAEs Grade 2 experienced by the same subject within one week (according to the CTCAE) including 2 symptomatic hypotension events within one week (non-urgent medical intervention indicated) or any Grade 3 hypotension event (medical intervention or hospitalization indicated) assessed by the PI. Two grade 2 injection site reactions such as presence of swelling at the injection site will not require urgent reporting to the DSMB or subject suspension as long as no further intervention was required.
- Prolongation of QTcF (QT corrected Fredericia) interval to more than 500 msec, ventricular tachycardia greater than five beats
- Any clinically significant worsening of existing disproportionate growth, as determined by physical measurement ratios and/or PI assessment based on measurement or clinical observation findings
  - o Sitting height to standing height ratio – Worsening of ratio of more than 1 standard deviation from initiation of therapy based on NHANES data .
  - o Arm span minus height – Worsening of more than 1 standard deviation since initiation of therapy with a SDS either >+2 or <-2. Data is based on Gerver et al.
- Excessively rapid increase in growth velocity (defined as greater than the 90th percentile on age- and gender-specific growth charts) sustained over a period of 2 years or associated with an adverse event such as joint pains or deformity 
- Clinically significant worsening of scoliosis as observed via clinical or radiographic assessment. This is defined as a new onset asymmetry noticed during a forward bend test or an increase in Cobb angle of >10 degrees from baseline or any Cobb angle of >20 degrees at any point in the study.

Subjects may continue in the extension phase of the study until achieving near final adult height which will be defined as either:

- A growth velocity <1.5 cm/year over the prior 12 months
- A bone age via the Greulich and Pyle method of 13 years in females and 15 years in males.

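### On-drug physical examinations are compared with the Screening examination six months before the first dose, so a non-serious finding that arose off drug may first be captured as an on-drug adverse event

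*Protocol*

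**What the plan says.** Section 8.2, Physical Examination and Tanner Staging, fixes one reference for every examination: "The Screening Visit results will be the baseline" values. It adds that "clinically significant changes from baseline will be recorded as an AE or SAE as appropriate".

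The Schedule of Activities (1.3) puts the Day 1 visit, at which vosoritide starts, 6 months (± 2 weeks) after Screening. Its row "Physical examination including a complete musculoskeletal exam" is marked at Screening, Day 1, Month 6, Month 12 and early termination. No section makes the Day 1 examination the reference for the later visits. Section 8.3.4 likewise treats conditions present at screening as baseline.

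Three statements bear on when an AE is captured:
- 8.2 (Adverse Events) has AEs assessed continuously from consent.
- 8.3.4 collects time of onset and records reportable events with start dates from consent onwards.
- The last sentence of 8.3.1 says that, between consent and the first dose, only SAEs associated with protocol-imposed interventions are reported.

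The primary safety hypothesis in 9.1 aims to rule out that "risk of adverse events post-drug administration will be more than twice the risk during the baseline period". Section 9.4.1 makes all comparisons self-controlled, with the observation period as the control.

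**The concern.** In a self-controlled design the observation period stands in for a control arm, so each event has to fall in the right period. With Screening as the only examination reference, a musculoskeletal or other finding that appears in the six untreated months and persists still qualifies as a change from baseline at Months 6 and 12. If it was not written down as an AE on Day 1, the 8.2 rule calls for it to be recorded at an on-drug visit. That adds an off-drug event to the treatment side of the 9.1 comparison and makes the drug look less safe than it is.

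Other parts of the protocol anchor on the start of treatment. Height SDS change runs from Visit Day 1 (8.1), and the sitting-height stopping rule in 7.1 reads "Worsening of ratio of more than 1 standard deviation from initiation of therapy". Different measures may properly have different references, so this is not a contradiction in itself. It does show that an anchor at the start of treatment is already in use.

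**Working it through.** The plan gives no figure on this point, so there is nothing to reproduce. The check is a reading of the text, followed by a bound on the size.

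**Text.** Take a non-serious, lasting finding absent at Screening, present on Day 1 and unchanged at Months 6 and 12.
- Under 8.2 and 8.3.4 it is an AE at Day 1 with onset before drug, and it belongs to the observation period.
- Under the last sentence of 8.3.1 it is not reported before drug. At Month 6 it is still a change from Screening, so 8.2 makes it an AE there.

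Which path is taken depends on which section staff follow.

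**Share of the comparison window that is off drug.** Inputs from 1.3: 6 months from Screening to Day 1, then 6 or 12 months on drug. Assumptions: constant rate of new lasting findings and no drug effect. Formula: off-drug time / (off-drug + on-drug time).
- Month 6: 6 / (6 + 6) = 50%. Moving Day 1 by ± 2 weeks (5.54 to 6.46 months off drug) gives 48% to 52%.
- Month 12: 6 / (6 + 12) = 33%, range 32% to 35%.

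Counting children rather than time, with an assumed risk p per half-year, the pre-drug share is p / [1 − (1 − p)²] at Month 6 and p / [1 − (1 − p)³] at Month 12. For p = 5% these are 51% and 35%; for p = 10%, 53% and 37%. The message is the same: about half and about a third.

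**Scale in children.** With the maximum of 75 subjects, expected numbers changed by Month 12 are 75 × [1 − (1 − p)³] against Screening and 75 × [1 − (1 − p)²] against Day 1. The values of p are assumed; the protocol gives none.

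| p per half-year | Against Screening | Against Day 1 |
|---|---|---|
| 2% | 4.4 | 3.0 |
| 5% | 10.7 | 7.3 |
| 10% | 20.3 | 14.2 |
| 20% | 36.6 | 27.0 |

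All of these are upper bounds on the distortion, because they suppose that no off-drug finding was recorded at Day 1 with its true onset.

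**The case against.** The strongest reply is that 8.2 decides when an examination change becomes an AE, not which period it belongs to. AEs carry an onset date, and AE review is scheduled at Screening, at the monthly calls and on Day 1. Section 9.4.5 expects AEs among the observation-period statistics. The 8.3.1 definition covers events not previously observed or pre-existing conditions that worsened, and a finding documented on Day 1 and unchanged later is neither. A Screening reference is also needed, since otherwise the control period could yield no examination AEs.

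Most of this stands. Where staff record the finding on Day 1, no bias arises. What remains is that 8.3.1 contradicts the recording rule for exactly these findings, and 8.2 then captures them on drug. An SAP may define treatment-emergent events, but it cannot restore an onset that was never recorded.

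The objection also disposes of two stronger readings.

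**That the choice of baseline alone carries the risk ratio past 2.** With p = 5%, a reader might divide 1 − 0.95³ = 14.3% by 5% and get 2.85, against 9.75% / 5% = 1.95 with a Day 1 reference. The 2.85 counts the same finding in both periods. If it was recorded before drug, its onset is pre-drug and the ratio stays at 1.95. If it was not recorded, the observation-period count for such findings is near zero and 2.85 cannot arise. The 1.95 itself reflects 12 months compared with 6.

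**That a Day 1 asymmetry would count towards the scoliosis stopping criterion.** Section 7.1 says "This is defined as a new onset asymmetry noticed during a forward bend test" but does not tie this to Screening or to 8.2. Spine X-rays start at Day 1 or Day 2, so a Cobb-angle change can only run from about the start of treatment. The text is unclear on which examination is meant; it does not establish the stronger claim.

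**Conclusion.** The point holds in a limited form. Screening is the only stated reference for examination changes, it precedes the first dose by six months, and the examination repeated on Day 1 is given no role as a reference. A non-serious off-drug finding may therefore first be captured on drug, mainly where the last sentence of 8.3.1 is followed. The resulting bias in the 9.1 comparison would run against the drug.

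Its size cannot be known from the protocol. The bounds of about half (Month 6) and a third (Month 12) rest on a constant rate, lasting findings, no drug effect and no recording at Day 1. It would be wrong to say that every off-drug finding becomes an on-drug AE. Severity is modest: examination findings are one route into AE recording, and 9.4.4 makes the end-of-study safety analysis descriptive.

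**What to change.** In 8.2, keep the Screening examination as the reference for the observation period, and name the Day 1 examination as the reference for AE recording at on-treatment visits. State that the Day 1 examination is done before the dose; the protocol says this only of vital signs and the pubertal check. Add that a finding present on Day 1 counts as an on-drug AE only if it later worsens.

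Reconcile 8.2, 8.3.1 and 8.3.4 on which AEs are recorded before the first dose. This step is needed as well, because a Day 1 reference alone would not restore observation-period events that were never recorded.

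Separately, 7.1 and 8.2 should be reconciled on which examination the new-onset asymmetry wording refers to. The clinical rule itself is for the investigators to settle.

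The cost is protocol and CRF wording. The Day 1 examination is already scheduled for every child.
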